# Long term cerebral and vascular complications after irradiation of the neck in head and neck cancer patients: a prospective cohort study: study rationale and protocol

**DOI:** 10.1186/1471-2377-14-132

**Published:** 2014-06-19

**Keywords:** Head and neck cancer, Cerebrovascular disease, Carotid artery, Radiation vasculopathy

## Abstract

**Background:**

Successful treatment options for cancer result in more young long-term survivors prone for long-term complications. Carotid artery vasculopathy is a potential long-term complication after radiotherapy of the neck, resulting in cerebrovascular events and probably deficits in cognitive and motor functioning. Better insight into the underlying pathofysiology of radiotherapy induced carotid artery vasculopathy is needed for prognostic purposes and to develop preventive strategies.

**Methods/Design:**

The current study is a prospective cohort study on the long-term cerebral and vascular complications after radiotherapy of the neck, in 103 patients treated for head and neck cancer, included in our study database between 2002 and 2008. Baseline protocol (before radiotherapy) included screening for cerebrovascular risk factors and intima media thickness measurement of carotid arteries by ultrasonography. Follow-up assessment more than 5 years after radiotherapy included screening of cerebrovascular risk factors, cerebrovascular events, neurological examination with gait and balance tests, extensive neuropsychological examination, self-report questionnaires, ultrasonography of the carotid arteries with measurement of intima media thickness and elastography, magnetic resonance imaging of the brain and magnetic resonance angiography of the carotid arteries.

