[8]. To assess this, all study patients underwent MRI of the brain to analyze silent brain infarcts and related pathology like white-matter lesions and cerebral atrophy.

The third question addresses the relation between RT and clinical outcome measures (motor and cognitive functioning, as well as quality of life; QoL). Silent brain infarcts are associated with gait disturbances, decline in cognitive function and increased risk of developing dementia
[9-11]. We performed quantitative gait/balance analysis and an extensive neuropsychological assessment in all patients. Finally, we want to study the relation between patient and treatment baseline characteristics and the development of vasculopathy, in order to find high risk patients that can benefit from preventive strategies.

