## Methods

The current study is a prospective cohort study that aims to investigate the frequency, pathophysiology and long-term outcome of radiotherapy induced vasculopathy. The Medical Ethics Review Committee region of Arnhem-Nijmegen approved the study (NL 41008.091.12).

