### Follow-up > 5 years after radiotherapy

At follow-up all patients underwent a structured program (Table 
1), consisting of assessment of demographics and life style, medical history and medication use, fasting laboratory investigation, electrocardiogram (ECG), physical and neurological examination, extensive neuropsychological assessment battery (NPA), carotid artery ultrasound (Intima Media Thickness measurement and elastography), MRI/MRA of the brain and carotid arteries, gait and balance analysis and self-report questionnaires.

**Table 1 T1:** Schedule of assessments

**Assessment**	**Baseline**	**Follow-up**

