## Results

103 patients who had sought medical attention at one of the two University Medical Centers between 2002 and 2008 fulfilled inclusion and exclusion criteria for our study. The number of patients lost to follow-up is reported in Figure 
1. 51 patients have been seen for the follow-up protocol more than 5 years after RT between November 2012 and November 2013. Another 14 patients underwent a telephone follow-up. Characteristics of our population at baseline and follow-up are reported in Table 
2.

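### The abstract and Background describe 103 patients and a complete follow-up battery, but only 51 were examined and 65 have any reported follow-up, so the denominators and the reach of the claims need restating

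*Protocol article*

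**What the plan says.** The abstract (Methods/Design) gives the cohort as "in 103 patients treated for head and neck cancer, included in our study database between 2002 and 2008" and goes straight on to the follow-up assessment: risk factors, events, gait and balance, neuropsychology, carotid ultrasound with elastography, brain MRI and carotid MRA. Neither 51 nor 65 appears there.

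The Background says "all study patients underwent MRI of the brain", and in its paragraph on the third question makes the same unqualified statement about gait/balance analysis and neuropsychological assessment. The section on follow-up more than 5 years after radiotherapy opens in similar terms: "At follow-up all patients underwent a structured program".

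The Results start from the same 103 but report that "51 patients have been seen for the follow-up protocol more than 5 years after RT between November 2012 and November 2013" and "Another 14 patients underwent a telephone follow-up". Losses are referred to a flow chart, and Table 2 is headed n = 65.

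Two stated uses of the data depend on the denominator. The Methods say that the study "aims to investigate the frequency, pathophysiology and long-term outcome of radiotherapy induced vasculopathy". The Controls section compares the frequency of silent brain infarctions and white matter lesions with that in published population-based studies.

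**The concern.** The positive statements that all patients were scanned and tested cannot stand beside 51 examined out of 103. A reader of the abstract would take 103 as the size behind the imaging, cognitive and gait findings, which is about twice the true maximum.

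The number matters, and so does who is in it. To be examined, a patient had to be alive, reachable and willing to attend more than 5 years after radiotherapy. A frequency in that group is a frequency among attending survivors. Setting it against a population reference, or using it to identify high-risk patients among those about to be irradiated, assumes that it carries over to the cohort as enrolled. The Discussion presents cohort size as a strength and lists no limitation about attrition or survival.

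**Working it through.** **Inputs.** Enrolled: 103 (abstract; Results). Examined: 51 (Results). Telephone only: 14 (Results). Table 2 heading: n = 65.

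**Reproducing the article's own figure.** 51 + 14 = 65, which matches Table 2. As a second check, the seven diagnosis percentages in Table 2 (45, 14, 15, 2, 17, 2, 6) correspond to 29 + 9 + 10 + 1 + 11 + 1 + 4 = 65 patients. Table 2 therefore describes those with follow-up contact and not the 103 enrolled.

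**Shares of the enrolled cohort.**

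| Group | Count | Share of 103 |
|---|---|---|
| Examined | 51 | 49.5% |
| Telephone only | 14 | 13.6% |
| Any follow-up contact | 65 | 63.1% |
| Not examined | 103 − 51 = 52 | 50.5% |
| No reported follow-up contact | 103 − 65 = 38 | 36.9% |

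MRI, ultrasound, elastography, gait and neuropsychology need a visit, so their base is at most 51. Event history can be asked by telephone, so its base is at most 65.

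**What the denominator does to precision.** The article reports no outcome frequency, so 20% is assumed here. The 95% half-width is 1.96 × √(p(1 − p)/n):
- n = 51: 1.96 × √(0.20 × 0.80/51) = 11.0 percentage points.
- n = 103: 1.96 × √(0.20 × 0.80/103) = 7.7 percentage points.

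**What the missing patients could do.** Suppose 10 of the 51 examined have a finding (assumption). If none of the 52 unexamined had it, the cohort frequency would be 10/103 = 9.7%. If all did, it would be (10 + 52)/103 = 60.2%. These are outer limits that treat every unexamined patient as having a value, which does not apply to anyone who had died.

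For events, assume a 10% risk among the 65 and k times that risk among the 38. The cohort risk is (65 × 0.10 + 38 × 0.10k)/103:
- k = 0: 6.5/103 = 6.3%.
- k = 1: 10.3/103 = 10.0%.
- k = 2: 14.1/103 = 13.7%.
- k = 3: 17.9/103 = 17.4%.

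The result can fall on either side of 10%, and nothing in the text fixes k.

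**The case against.** The strongest reply is that nothing is concealed. One Results paragraph gives 103, 51 and 14, the flow chart is cited for losses, and Table 2 carries its own n. No single sentence says that all 103 were fully assessed. In the abstract, 103 is the number entered in the database, and the opening of the follow-up section can fairly be read as meaning those who attended. This stands as far as it goes, but it does not cover the Background, whose statements about MRI, gait and neuropsychology carry no such qualifier, nor the abstract's silence on 51 and 65.

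It is also fair to say that the article is framed around long-term survivors, so a frequency among survivors is a legitimate target for imaging and cognition. Likewise, the within-patient change in intima media thickness remains valid for those measured twice; there, selection limits only generalisation.

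A reader might go further in four ways that the documents do not support:
- **The frequencies are too low because patients with fatal or disabling stroke dropped out.** This is plausible, but the vital status of the 38 and the reasons for loss are not in the text and the flow chart is not shown. Disabled patients may also be among the 14 telephoned.
- **Follow-up ran from about 4 to 12 years.** That follows only from the calendar limits of enrolment and visits. The article states more than 5 years, with a mean of 6.7 and SD of 1.2.
- **The planned tests are wrong for stroke.** The Statistical analysis section assigns methods by type of variable and never names a method for cerebrovascular events. Such detail may sit in a fuller document.
- **Half of the cohort is missing for every outcome.** Half is right for the examinations; for event history the base is nearly two thirds.

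**Conclusion.** The point holds as an internal contradiction with consequences for the denominators and for the reach of the claims. The imaging, cognition and gait outcomes, including the silent-infarct and white-matter-lesion frequencies set against population studies, rest on at most 51 of 103 patients (49.5%). Interview-based events rest on at most 65 (63.1%). Both groups are selected for being alive and reachable more than 5 years after radiotherapy.

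The counts come straight from the article and need no assumption. The precision and missing-patient illustrations rest on assumed frequencies and risk ratios, and show only that the unfollowed patients are numerous enough to matter. Neither the existence of a material bias nor its direction can be established from the text, so the article should not be charged with a known underestimate or with an erroneous event analysis.

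**What to change.** 1. In the abstract, state 103 enrolled, 65 with any follow-up and 51 examined.
2. In the Background and the follow-up section, replace the unqualified references to all patients with the 51 patients seen.
3. Give the denominator for each outcome.
4. Add a table comparing examined (51), telephoned (14) and not-followed (38) patients on the baseline data already collected, such as age, diagnosis, vascular risk factors and intima media thickness.
5. Limit frequency and risk-factor claims, including the comparison with population studies, to attending survivors of more than 5 years.
6. Where dates of events, death and last contact are already held, report stroke/TIA from radiotherapy as a cumulative incidence with death as a competing event. A new record search confined to the 38 should not be added lightly: the 65 were contacted directly, so ascertainment could differ between the groups.
7. Keep any inverse-probability weighting as a sensitivity analysis restricted to patients known to be alive. Weighting the 51 up to all 103 would assign imaging and cognitive values to patients who may have died.

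Items 1 to 5 cost wording and one table. Items 6 and 7 need some further analysis and depend on what dates and vital status are held. The price is a less favourable stated size, narrower claims and, if weighting is used, wider intervals.

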**Discussion:**

The current study adds to the understanding of the causes and consequences of long-term cerebral and vascular changes after radiotherapy of the neck. These data will be helpful to develop a protocol for diagnostic and preventive strategies for long-term neurological complications in future head and neck cancer patients with anticipated radiotherapy treatment.

## Background

Successful treatment options for cancer have resulted in more long-term survivors, prone to long-term complications of chemotherapy and radiotherapy (RT). A well-known long-term complication of RT of the neck is carotid artery vasculopathy, which ultimately can lead to stroke
[1,2].

Apart from acute neurological complications, like a cerebral infarction, evidence from daily clinical practice shows more subtle, slowly progressive deficits in cognitive and motor functioning. These long-term cerebral and vascular complications in young survivors of cancer are a serious potential problem that hamper reintegrating in social functioning and work. The longer survival stresses the need for a long-term follow-up study that assesses the long-term complications of RT induced carotid artery vasculopathy. To date, no such studies exist to the best of our knowledge.

We hypothesize that RT of the neck accelerates carotid atherosclerosis with secondary development of cerebral vascular lesions. These vascular cerebral changes are subsequently related to cognitive and motor functioning with a major impact on activities of daily social functioning. A better understanding of the underlying pathophysiology of this RT induced vasculopathy is needed for prognostic purposes and can be used to develop strategies that prevent further progression and thereby reducing the risk of future stroke and neurological impairments.

The current study aims to investigate four questions. The first question focuses on the relation between RT and long-term carotid artery-wall changes. We hypothesize that irradiation induces premature atherosclerosis which is different from more common atherosclerosis due to classic cerebrovascular risk factors. We therefore study the location and composition of post-irradiation vessel-wall changes with advanced imaging techniques; plaque and Intima Media Thickness (IMT) analysis on ultrasound with innovative vessel-wall elastography and magnetic resonance imaging/angiography (MRI)/(MRA)
[3-5]. The second question examines the relation between RT and long-term cerebral vascular changes. In the general population the prevalence of silent brain infarcts (SBI) is up to fivefold higher than that of acute stroke
[6]. SBI are related to impaired cognitive functioning, dementia, stroke and gait and balance disorders
[7]. Carotid artery pathology increases the risk of SBI
[8]. To assess this, all study patients underwent MRI of the brain to analyze silent brain infarcts and related pathology like white-matter lesions and cerebral atrophy.

The third question addresses the relation between RT and clinical outcome measures (motor and cognitive functioning, as well as quality of life; QoL). Silent brain infarcts are associated with gait disturbances, decline in cognitive function and increased risk of developing dementia
[9-11]. We performed quantitative gait/balance analysis and an extensive neuropsychological assessment in all patients. Finally, we want to study the relation between patient and treatment baseline characteristics and the development of vasculopathy, in order to find high risk patients that can benefit from preventive strategies.

## Methods

The current study is a prospective cohort study that aims to investigate the frequency, pathophysiology and long-term outcome of radiotherapy induced vasculopathy. The Medical Ethics Review Committee region of Arnhem-Nijmegen approved the study (NL 41008.091.12).

### Patients

A prospective cohort study of head and neck cancer patients in two centers of the Netherlands (the Netherlands Cancer Institute/Antoni van Leeuwenhoek Hospital (NCI/AvL), Amsterdam and the Radboud University Medical Center Nijmegen) was initiated.

At baseline, patients were eligible for inclusion if they received RT of the neck because of a T1/T2 (N0M0) laryngeal carcinoma, T1/T2 (N0M0) parotid carcinoma/pleomorphic adenoma, T1/2 (N1/2 M0) naso/oro/hypopharynxcarcinoma or non-Hodgkin/Hodgkin lymphoma. Originally, the study was designed as an open-label multicentre Prospective Randomized Open Blinded Endpoint (PROBE) study to assess the effect of an HMG-coA reductase inhibitor (atorvastatine) on carotid IMT in the first 2 years after irradiation of the neck. Because of dwindling accrual the study was redesigned to a prospective cohort study. The initial exclusion criteria were: a history of cerebrovascular disease, pregnancy or breast-feeding, ongoing treatment with an HMG-coA reductase or cytochroom P450 inhibitor, active liver disease or > 3 times the upper limit of serum transaminases, 5 times the normal level of creatine phosphokinase, serum cholesterol > 7 mmol/L and a life expectancy < 2 years. All patients gave written informed consent.

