### Controls

The IMT measurements will be compared to the baseline measurements and the elastography measurements will be compared to an age and sex matched control group of patients who had a stroke and at least one of the following cerebrovascular risk factors: hypertension, diabetes, smoking, hypercholesterolemia and atrial fibrillation. The cognitive performances of all patients will be compared to available normative reference values (adjusted for age and education level). Finally, the frequency of silent brain infarctions and white matter lesions will be compared to the frequency in patients without RT of the neck, as described in prior population based studies
[12,13].

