### Outcome events

#### Imaging outcomes

Firstly, on ultrasonography, the IMT of the carotid artery 6 years after RT will be compared with the IMT at baseline. Furthermore, the strain in the vessel wall and plaque 6 years after RT will be measured and compared with a control group. Secondly, on MRI/A of the carotid arteries the degree of stenosis, location and when possible composition of vessel wall changes (lipids, fibrosis, hemorrhage) will be scored, according to an in house developed protocol.

All MRIs of the brain will be scored semi-quantitatively by two neuroradiologists separately for white-matter lesions (WML), brain atrophy and (silent) brain infarctions using validated scales
[34-36] and in case of disagreement a consensus meeting will be held.

Furthermore, total white matter lesion volume will be calculated by a prior published, in-house developed, validated technique
[37]. In short, WML are defined as hyperintensive lesions on FLAIR MRI without corresponding cerebrospinal fluid like hypo-intense lesions on the T1 weighted image. Gliosis surrounding lacunar and territorial infarcts is not considered to be WML. Finally, brain volumetry will be done to measure total white and grey matter volumes. Grey and white matter tissue and cerebrospinal fluid probability maps will be computed by using a six class segmentation tool in Statistical Parametric Mapping Software (http://www.fil.ion.ucl.ac.uk/spm) (SPM 8) on the T1 MPRAGE images. Total grey and white matter volumes are calculated by summing all voxel volumes belonging to the tissue class. Total brain volume is taken as the sum of total grey and total white matter volume. Co-registration parameters of the FLAIR image to the T1 image are computed (SPM8 mutual information co-registration) and used to bring both the FLAIR and WML segmentation images into the subjects (anatomical) reference frame. Transformed images will visually be checked for co-registration errors. Subsequently, the WML segmentations are re-sampled to and combined with the white matter maps to yield to a WML map (the intersection of WML and white matter) and NAWM map (the complement of WML in white matter) in the T1 reference space.

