### Statistical analysis

Analysis of continuous variables will be done with Student’s *t* test or analysis of (co)variance or in case of skewed distributions which cannot be normalized by log transformation corresponding nonparametric tests will be used. Chi-squared test will be used for analysis of categorical variables and logistic regression analyses will be used to adjust for potential confounding factors.

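### The cohort grew out of a randomised atorvastatin study with carotid IMT as endpoint, but the IMT analysis never uses the allocation, so any treated patients could dilute the reported increase

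*Protocol article*

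**What the plan says.** All references are to the protocol article.

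- **Origin (Patients).** "Originally, the study was designed as an open-label multicentre Prospective Randomized Open Blinded Endpoint (PROBE) study", with the aim "to assess the effect of an HMG-coA reductase inhibitor (atorvastatine) on carotid IMT in the first 2 years after irradiation of the neck". Then: "Because of dwindling accrual the study was redesigned to a prospective cohort study". The number randomised, the number given atorvastatin and the duration of treatment are not stated.
- **Entry criteria (Patients, Results).** The initial exclusions are those of a statin trial (liver enzymes, creatine phosphokinase, high cholesterol) and include "ongoing treatment with an HMG-coA reductase or cytochroom P450 inhibitor". The Results section says the 103 patients met the inclusion and exclusion criteria.
- **IMT contrast (Controls, Imaging outcomes).** "The IMT measurements will be compared to the baseline measurements", and again "the IMT of the carotid artery 6 years after RT will be compared with the IMT at baseline". There is no unirradiated comparison group for IMT.
- **Analysis (Statistical analysis).** "Analysis of continuous variables will be done with Student’s" *t* test, analysis of (co)variance or a nonparametric equivalent. For confounding, "logistic regression analyses will be used to adjust for potential confounding factors". No covariate is named.
- **Statin data (Table 1, Medical history and medication use).** Statin use is collected by questionnaire and marked at follow-up only. Table 2 reports neither statin use nor allocation.

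**The concern.** The former trial endpoint now answers the first study question, on radiotherapy and the carotid wall. The authors chose atorvastatin because it might alter that endpoint, and the Discussion still names statins as a possible preventive strategy. If some patients took it for up to two years under allocation, the pooled change averages treated and untreated courses. If the drug slows thickening, the average lies below what untreated irradiated patients would show.

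Statin use at follow-up does not repair this, for two reasons:

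- It may miss a course that ended years before.
- It may be driven by what happened after radiotherapy. Table 2 has hypercholesterolaemia rising from 9% to 39%, so later prescribing by indication is likely to be mixed in.

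At stake is the size of the IMT increase and the power to detect it in the 51 patients seen at follow-up.

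**Working it through.** The article gives no sample size calculation, effect size or standard deviation for IMT, so there is no stated figure to reproduce. The check has two parts.

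**1. Was there a treated phase, and would the plan show it?**

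- Accrual that dwindles had begun. The only exclusion criteria listed are the initial ones, and all 103 patients are said to meet the criteria. This suggests recruitment under the trial's rules, but does not prove that anyone was treated.
- Current statin users were excluded at entry, so any allocated atorvastatin would have been new exposure.
- Follow-up averages 6.7 years after radiotherapy (Table 2, n = 65, including 14 telephone contacts). A two-year course begun at radiotherapy would have ended about 6.7 − 2 = 4.7 years before the medication questionnaire.
- The article is silent on allocation after the Patients section, although Table 2 reports items such as migraine and abdominal circumference.

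**2. How large could the dilution be?** This is an illustration; *f* and *r* are not in the documents.

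Let *f* be the share of followed patients who took atorvastatin and *r* the proportion by which it reduces their IMT change at follow-up. Then

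observed mean change / untreated mean change = 1 − *f* × *r*.

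| *f* | *r* = 0.10 | *r* = 0.25 | *r* = 0.50 |
|---|---|---|---|
| 0 | 1.00 | 1.00 | 1.00 |
| 0.10 | 0.99 | 0.975 | 0.95 |
| 0.25 | 0.975 | 0.938 | 0.875 |
| 0.50 | 0.95 | 0.875 | 0.75 |

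With *r* = 0 every row is 1.00.

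Approximate power of a paired test with n = 51, two-sided alpha 0.05 (assumed) and standardised untreated change *d* = 0.4 (assumed) is Φ(*d* × ratio × √51 − 1.96), with √51 = 7.14:

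- ratio 1.00: Φ(2.86 − 1.96) = 82%
- ratio 0.95: Φ(2.71 − 1.96) = 77%
- ratio 0.875: Φ(2.50 − 1.96) = 71%
- ratio 0.75: Φ(2.14 − 1.96) = 57%

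**Does separating the groups recover the untreated change?** A simulation of 5,000 studies used 25 of 51 patients exposed, *r* = 0.5, an untreated change of 1 and a standard deviation of 2. The pooled mean was 0.75 (standard error 0.28). The mean in the 26 unexposed was 0.99 (standard error 0.39). The ratio of standard errors is 0.39 / 0.28 = 1.4, which agrees with √(51/26) = 1.40.

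The restricted analysis corrects the estimate but does not regain power. With n = 26 and *d* = 0.4, power is Φ(0.4 × √26 − 1.96) = Φ(0.08) = 53%, close to the 57% of the diluted analysis.

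**The case against.** The strongest reply is that nothing shows a treated patient among the 103 or the 51, so no bias is demonstrated. That stands. A reader might infer from the study's history that the IMT result is biased; the documents support only that it may be.

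Second, a condensed article commonly leaves its covariate list to a fuller plan, and unnamed confounders could include statin exposure. This stands as far as covariates go. It does not cover the number of patients randomised or treated, which is a fact about the cohort. Nor does it change the stated IMT contrast, which is a single pooled change.

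Third, blank baseline cells in Table 1 prove little: diabetes, hypercholesterolaemia and obesity are also blank there, although the Baseline section says they were assessed. That is fair. Statin users were excluded at entry anyway. The point rests on the years between baseline and follow-up, for which the article describes no statin record.

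Fourth, some larger claims might be drawn and should not be:

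- **Confounding of the baseline-predictor question.** Randomised allocation is independent of baseline factors in expectation. It adds noise, chance imbalance or effect modification, not systematic confounding.
- **Allocation as a covariate in every model.** Allocation cannot confound a one-group mean change; it shifts that mean. Strain is compared with stroke patients, and brain lesions with published populations, neither of which has an allocation.
- **IMT as the primary outcome.** The article ranks no outcome as primary.
- **A loss of half the IMT change.** This would need half the patients treated and a drug that abolishes all thickening, with the effect lasting years beyond the course. No figure in the documents supports it.

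**Conclusion.** The point holds in a limited form. The cohort derives from a randomised atorvastatin study with IMT as endpoint, the stated IMT analysis pools all patients, and neither the allocation nor early exposure is used. If any analysed patient was treated and the drug slows thickening, the increase after radiotherapy may be understated.

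The size cannot be computed from the documents. Under the assumed ranges (*f* from 0 to 0.5, *r* from 0 to 0.5) the observed change is 100% down to 75% of the untreated change. At an assumed *d* of 0.4, power falls from 82% to 57% at the extreme. With no treated patients or no lasting drug effect, nothing changes. The article's text does not settle which case applies.

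**What to change.** 1. Take the original allocation and the actual start and stop dates of atorvastatin from the existing trial database. Report the number in each category (atorvastatin, control, not randomised) in Table 2. If nobody was treated, one sentence saying so closes the point.
2. If any were treated, report the baseline-to-follow-up IMT change by allocation, and include allocation as a term in any regression of IMT change.
3. Repeat the main IMT analysis without patients allocated to atorvastatin. As a sensitivity check, do the same for the strain and brain imaging comparisons.
4. Do not use statin use at follow-up as a substitute for allocation. Statins started later by indication are a separate, non-random exposure that these steps do not remove.

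**Cost.** A database look-up, one or two degrees of freedom in the regressions, and one restricted analysis. Its standard error is about 1.4 times larger if half of the 51 were treated, and less if fewer were. It should be read for the estimate rather than for its *p* value.
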